## Abstract

**Background:**

Human milk (HM) is the ideal source of nutrients for infants. Its composition is highly variable according to the infant's needs. When not enough own mother's milk (OMM) is available, the administration of pasteurized donor human milk (DHM) is considered a suitable alternative for preterm infants. This study protocol describes the NUTRISHIELD clinical study. The main objective of this study is to compare the % weight gain/month in preterm and term infants exclusively receiving either OMM or DHM. Other secondary aims comprise the evaluation of the influence of diet, lifestyle habits, psychological stress, and pasteurization on the milk composition, and how it modulates infant's growth, health, and development.

**Methods and design:**

NUTRISHIELD is a prospective mother-infant birth cohort in the Spanish-Mediterranean area including three groups: preterm infants <32 weeks of gestation (i) exclusively receiving (i.e., >80% of total intake) OMM, and (ii) exclusively receiving DHM, and (iii) term infants exclusively receiving OMM, as well as their mothers. Biological samples and nutritional, clinical, and anthropometric characteristics are collected at six time points covering the period from birth and until six months of infant's age. The genotype, metabolome, and microbiota as well as the HM composition are characterized. Portable sensor prototypes for the analysis of HM and urine are benchmarked. Additionally, maternal psychosocial status is measured at the beginning of the study and at month six. Mother-infant postpartum bonding and parental stress are also examined. At six months, infant neurodevelopment scales are applied. Mother's concerns and attitudes to breastfeeding are registered through a specific questionnaire.

**Discussion:**

NUTRISHIELD provides an in-depth longitudinal study of the mother-infant-microbiota triad combining multiple biological matrices, newly developed analytical methods, and *ad-hoc* designed sensor prototypes with a wide range of clinical outcome measures. Data obtained from this study will be used to train a machine-learning algorithm for providing dietary advice to lactating mothers and will be implemented in a user-friendly platform based on a combination of user-provided information and biomarker analysis. A better understanding of the factors affecting milk's composition, together with the health implications for infants plays an important role in developing improved strategies of nutraceutical management in infant care.

**Clinical trial registration:**

https://register.clinicaltrials.gov, identifier: NCT05646940.

## Introduction

1.

Breastfeeding (BF) is the optimal feeding practice for all infants, associated with numerous health benefits for the mother–infant dyad, as well as, being an ecologic practice (1). The World Health Organization highly recommends exclusive BF for all infants up to six months, born either full–term (2, 3) or prematurely (4). Human Milk (HM) is a dynamic fluid that meets the offspring's needs (5–8), and is ample in nutrients and bio-active compounds intended to enhance immunity and growth (9). HM also hosts a complex ecosystem of microbiota (10), which is of paramount importance for the offspring's immunity (5).

During the last decades, the incidence of preterm deliveries (<37 weeks of gestation) and survival rate of preterm infants (PI) have been steadily increasing (11), hand in hand with the interest in preterm and early infant nutrition. Associated birth complications are the leading cause of death among children under five years of age, responsible for ∼1 million global deaths per year (12). Progress in medical interventions has allowed to enhance survival of an increasing proportion of extremely low gestational age newborns and low birth-weight infants. Early infant nutrition has become a major player in improving clinical outcomes of survivors (13). HM is recommended for PI based on an impressive array of benefits provided to this highly vulnerable population, including ameliorated immunological and gastrointestinal outcomes (14–20). Optimal growth in the postnatal period is challenging dure to increased nutritional demands and metabolic and digestive immaturity of PI. Greater weight gain is associated with better neurodevelopment outcomes (21).

In situations where mothers are unable to produce sufficient milk quantities to exclusively or partially breastfeed, pasteurized donor human milk (DHM) is a viable option to avoid formula feeding, especially for low birth-weight children (22). DHM is a valuable but limited resource and Human Milk Banks prioritize its distribution to the patients with highest risk of necrotizing enterocolitis, generally PI <32 weeks of gestation or with a birthweight <1,500 g (3, 23). To date, most studies focus on the benefits of using DHM over formula in PI, when own mother's milk (OMM) is limited or unavailable. There is clear evidence of the superiority of OMM against formula (24); however, although DHM apparently protects against necrotizing enterocolitis as compared to formula, results are not conclusive (25) and there are only few reports directly comparing DHM and OMM. While providing some bioactive agents, DHM consumption is associated with slower growth rates in comparison to the administration of OMM or formula (24). This finding may be attributable to several factors. Most DHM is provided by women who have delivered at term and donate their milk in later stages of lactation up to several months after delivery. The effect of gestational age on HM composition has been reported to affect a wide array of compounds including lipids (26), lactoferrin (27), amino acids (28), and HM oligosaccharides (29). In comparison to preterm milk during the first weeks after delivery, studies on the mean composition of DHM show a lower content in total protein, fat, and other bioactive molecules (30). Its composition is also affected by the processing of expressed milk, including stringent protocols applied in HM banks, i.e., pasteurization, freezing, and storage (31, 32), necessary to reduce the potential risk to transmit infectious agents.

Beyond the physiological adaptations, research has focused on the potential effects of the maternal diet on the HM composition. In an earlier report, HM composition was found rather different among mothers of diverse ethnic backgrounds, with different dietary habits (33). The fatty acid profile of HM varies in relation to maternal diet, particularly, in the long chain polyunsaturated fatty acids (LCPUFAs) (31, 32, 34, 35). Additionally, in a recent comprehensive systematic review of 104 observational and interventional studies, HM composition was found to relate to the maternal consumption of fatty acids, fat-soluble vitamins, and vitamin B1 and C intake (36, 37). No similar relationships were found for dietary intake of iron, folate, calcium, selenium, or proteins (36).On the contrary, another recent systematic review determined that information regarding the relationship between dietary patterns during lactation and HM content is insufficient for total fat, vitamins B and C, and choline content and inexistent for total proteins, macronutrient distribution, human milk oligosaccharides (HMOs), vitamins A, D, E and K, iodine, and selenium (38). Hence, more studies are needed to conclude for several nutrients and little is known on how the maternal diet may also affect non-nutritive constituents of HM, e.g., prebiotics content (39) or microbiota (40, 41). Finally, existing evidence comes mainly from studies on full-term infants (TI); the impact of maternal nutrition on the composition of HM for the preterm offspring has not been adequately documented.

Therefore, the main objective of this study is to compare the % weight gain/month in PI and TI exclusively receiving either OMM or DHM. In addition, secondary objectives are (i) to evaluate associations between the mother's diet, physical, and psychosocial status (e.g., lifestyle, perceived stress, anxiety, and depression) and HM composition in PI and TI, (ii) to evaluate the effect of pasteurization/storage on DHM composition, (iii) to assess the interplay of microbiota and microbiota activity and HM composition, (iv) to assess the interplay of microbiota and microbiota activity detected in HM and PIs and TIs, (v) to evaluate the impact of microbiota and microbiota activity on the vitamin status of PIs and TIs, (vi) to test the performance of novel sensor devices developed within this project, and (vii) the development of a personalized nutrition algorithm for lactating mothers.

## Methods and analysis

2.

### Study design

2.1.

The NUTRISHIELD study is a parallel group, non-randomized, observational study performed at the Division of Neonatology of the University & Polytechnic Hospital La Fe (HULAFE), including TI and PI and their mothers, covering the period from birth to 24 months of infant's age. In addition, mothers providing DHM to study participants are also included.

The study protocol has been approved by the Scientific and Ethics Committee for Biomedical Research (CEIm) of the HULAFE (#2019-289-1). All methods have been performed in accordance with the relevant guidelines and regulations and written permission has been obtained from mothers or legal representatives by signing an informed consent form.

Confidentiality of subjects is maintained during the study. All participants have been assigned a code and data allowing personal identification will not be shared at any time. Participants may withdraw consent for participating in the study at any time.

### Study population and recruitment

2.2.

Participants were recruited at the end of pregnancy (when admitted to the obstetric ward) or within one week after birth in case of hospitalized infants at HULAFE. Recruitment started in October 2020 and was completed in July 2022. Three mother-infant groups were enrolled, i.e., PI fed with OMM (PI-OMM), PI fed with pasteurized DHM (PI-DHM), and TI receiving OMM (TI-OMM), and their mothers.

The inclusion criteria were (i) acceptance of the mother to participate and sign an informed consent form, (ii) a gestational age <32 weeks for the group of PI and >37 weeks for the group of TI, and (iii) exclusive consumption (i.e., >80% of total intake) of either OMM or DHM at time point CEN (complete enteral nutrition, 150 mL/Kg/day) for PI or RBW (recovery of birth weight) for TI. Although the type of feeding of PIs included in either group (PI-OMM or PI-DHM) may have changed at later time points, they remained in the same study group, so the effect of feeding of each type of milk at CEN and its long-term effects can be studied. Likewise, the use of infant formula and the initiation of weaning at later time points was recorded without affecting follow-up assessments. The exclusion criteria were (i) non-compliance with any of the inclusion criteria, (ii) the requirement of a special diet for the mother (e.g., celiac disease, diabetes) or maternal consumption of probiotics, (iii) the need of intestinal surgery, severe congenital malformations, or chromosomopathies of the infant, (iv) mother's residence outside the Valencian Community and (v) severe language barriers hampering the collection of necessary data from mothers not speaking Spanish and/or English.

Sample size estimation was performed for the primary outcome (i.e., % weight gain/month from birth until hospital discharge of PI fed with DHM and OMM) and was based on result of a previous study (42). Considering the median % weight gain/month (interquartile range, IQR) of 52% (IQR: 30) in the PI-DHM group and 63% (IQR: 21) in the PI-OMM, 18 infants per group were needed to achieve a power of 90% with an alpha error of 5% between the % weight gain/month of PI exclusively receiving either OMM or DHM at CEN.

On the other hand, HM donors were recruited during their regular visits at the hospital's HM Bank of the Valencian Community. All participants met ordinary criteria for HM donation (e.g., negative screening results of a series of transmissible diseases, toxic habits, or some chronic medication) and accepted to sign an informed consent form and participate in the study.

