## Results and discussion

3.

Figure 4 summarizes the recruitment process, including the eligible PI (*n* = 104), excluded (*n* = 49), lost to follow up (*n* = 10) and the number of PI that were finally included in the study (*n* = 45). In addition, a control group comprising 31 full term OMM infant-mother dyads was recruited, with five participants being lost during follow-up. Altogether, a total of 71 infant-mother dyads were included and completed the study (28 PI-OMM, 17 PI-DHM and 26 TI-OMM), after losing 15 infant participants during follow-up. In total 662 urine, 594 faeces, 134 buccal swab, 33 venous and arterial cord blood, and 234 HM samples, as well as aliquots from 147 DHM batches before and after pasteurization have been collected. An ample array of laboratory methods for biomarker analysis and screening of biological samples and three *ad-hoc* designed sensors were developed. Currently, the analysis of all collected study samples is in progress at the different participating institutions.

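### On the plan's own medians and IQRs, 18 infants per group gives about 38% power for the primary comparison, not 90%; about 65 per group would be needed

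*Protocol article*

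**What the plan says.** Section 2.2 of the Protocol article (Study population and recruitment) sizes the study on "weight gain/month from birth until hospital discharge of PI fed with DHM and OMM". The planning values, taken from a previous study, are medians and interquartile ranges: "52% (IQR: 30) in the PI-DHM group" and "63% (IQR: 21) in the PI-OMM" group. From these the article states that "18 infants per group were needed to achieve a power of 90% with an alpha error of 5" per cent. It gives no SD, no conversion from IQR to SD, no sidedness and no test for this calculation.

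Section 2.7 (Statistics and data integration) names Student's t-test or the Wilcoxon rank-sum test, at a significance level of 0.05, for between-group comparisons of continuous measures. Section 3 (Results and discussion) reports the dyads that completed the study as "28 PI-OMM, 17 PI-DHM and 26 TI-OMM".

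**The concern.** The article prints both the inputs and the answer, and they look incompatible. An 11-point difference against IQRs of 30 and 21 is a moderate standardised effect. Eighteen per group at 90% power would require a standardised effect of about 1.1.

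The comparison is the study's main objective, and the Introduction says that few reports compare donor milk and own mother's milk directly. If the power is overstated, a non-significant result may be read as showing that the two milks support equal growth, when the study had little chance of detecting the difference it was planned on. The limitations in section 3 mention lost samples and the need for confirmation in a larger cohort, but not low power for the primary comparison.

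**Working it through.** **Inputs.** From section 2.2: medians 52 and 63, IQRs 30 and 21, 18 per group, power 90%, alpha 5%. From section 2.7: t-test or rank-sum test. Assumptions made here: roughly normal data, and a two-sided test unless stated otherwise.

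**Step 1: convert IQR to SD.** For normal data, SD = IQR/1.349.
- Donor milk: 30/1.349 = 22.24
- Own mother's milk: 21/1.349 = 15.57
- Root mean square: √[(22.24² + 15.57²)/2] = 19.19
- Difference: 63 − 52 = 11; standardised effect 11/19.19 = 0.573

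**Step 2: try to reproduce 18 per group.** By the normal approximation, n = 2 × (1.960 + 1.282)² × 19.19²/11² = 64 per group. With the noncentral t distribution it is 65 (pooled) or 66 (Welch). With the rank-sum test it is about 69 to 70. The stated 18 is not reproduced.

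**Step 3: power at 18 per group.** The standard error is √(22.24²/18 + 15.57²/18) = 6.40, so the expected difference is 11/6.40 = 1.72 standard errors.

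| Method, 18 per group | Power |
|---|---|
| Normal approximation, two-sided | 40.5% |
| Pooled t-test, two-sided | 38.6% |
| Welch t-test, two-sided | 38.4% |
| Rank-sum test, two-sided (simulated) | about 37% |
| Pooled t-test, one-sided 5% | 51.6% (53 per group needed for 90%) |

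**Step 4: look for a reading that gives 90%.**
- Smaller IQR (21) used for both groups: 54% power by t-test; 44 per group needed.
- SD taken as IQR/2: 70% power; 31 per group needed.
- Other shapes with the stated medians and IQRs (uniform, logistic, Laplace, log-normal): 25% to 56% with the t-test and 31% to 47% with the rank-sum test.
- A common SD of 9.9 would give 90% power at 18 per group by t-test. The IQRs imply 19.2, which is 1.9 times larger.
- SD taken as IQR/2.7 (pooled SD 9.6), half the proper value, brings the t-test requirement down to about 18 per group, with 91.6% power at 18. A halved SD is therefore a possible source of the figure, but the article does not say how it was derived.

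**Step 5: the infants who completed the study (17 donor milk, 28 own milk).**
- Standard error: √(22.24²/17 + 15.57²/28) = 6.14
- Power for 11 points: about 41% (Welch)
- Detectable difference: 17.9 points with 80% power, 20.7 points with 90%
- Expected 95% confidence interval half-width: about 12.6 points. An observed difference of exactly 11 would have an interval of about −2 to +24.

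**The case against.** Four points can fairly be made for the plan.

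**The conversion assumes normality.** The article gives medians and IQRs and never claims normal data, so 38% is not exact. This stands as a caveat. It does not rescue the claim, because the shapes tried range from 25% to 56%.

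**The 17 and 28 may not be the denominators for the primary outcome.** They are dyads that completed follow-up, whereas the primary outcome ends at hospital discharge. Section 3 gives 104 eligible preterm infants, of whom 49 were excluded and 10 lost, so 104 − 49 = 55 could have discharge weights. The text does not give the group split of those 10. This stands: the figures for 17 and 28 should be labelled as completers, and a donor-milk count below 18 is established only for them. If all 10 contributed, with the most favourable split (27 and 28), power would reach about 55%, still far short of 90%.

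**Welch's test is not named in the article.** At 17 and 28, Student's pooled t-test gives about 48% and the rank-sum test about 42%. The pooled figure is flattering, because the larger SD lies in the smaller group and simulation puts the type I error at about 7%.

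**The halved SD is conjecture.** Agreed. One-sided testing at 80% power with SD = IQR/2 also gives 18, although that contradicts the stated 90%. A misprinted input is possible too. The finding does not depend on which explanation is right.

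**Conclusion.** The concern holds. The stated 90% power does not follow from the inputs printed beside it. With SD = IQR/1.349 and a two-sided 5% test, 18 per group gives about 38% power, and 90% needs 65 to 66 per group by t-test, about 3.6 times the stated number. The planned 11-point difference would be missed about 60% of the time.

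The exact power depends on approximate normality and on sidedness, but no shape or sidedness tried comes near 90%. For completers, power is about 41%; it would be at most about 55% if every preterm infant lost to follow-up had a discharge weight. This must be corrected: it concerns the primary outcome, the discrepancy is large, and nothing else in the article puts it right.

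**What to change.** Recruitment closed in July 2022, so the change is to the text only.

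1. In section 2.2, correct the statement: with the cited medians and IQRs, and SD taken as IQR/1.349, 90% power at two-sided 5% needs about 65 infants per group, and 18 per group gives about 38%. State the test, the sidedness and the conversion. If an input was misprinted, correct it and show the calculation again.
2. State the achieved precision: for completers (28 own milk, 17 donor milk), power for 11 points is about 41% and the difference detectable with 80% power is about 18 points. If more infants have discharge weights, recompute with those counts.
3. Report the primary comparison as an estimate with a 95% confidence interval, and state that a non-significant result will not be read as no difference. Add low power for the primary comparison to the limitations in section 3.

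The cost is a few sentences and a less favourable power statement.

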### Assessment points and biological samples

2.3.

Samples from lactating mothers and their infants are collected at different timepoints, as shown in Figure 1. At birth, cord blood, and urine, and faeces from both infants and mothers are collected when possible. When PIs achieve CEN and TIs RBW, as well as one, two, three, and six months after delivery, urine and faeces from mothers and infants, as well as, HM from lactating mothers, are collected. Infants' and mothers' buccal swabs are collected at month six. During hospitalization of participants, samples are collected at the hospital by healthcare providers. After discharge, samples are collected at home and either transported to the hospital by study participants or staff of the NUTRISHIELD study. Mothers receive Standard Operation Procedures (SOPs) with detailed instructions and all the required material for sample collection at home. Additionally, hospital's staff instructs mothers on how to collect and store samples correctly.

**Figure 1 F1:**
[figure not shown]
Design of the NUTRISHIELD study. PI, preterm infant; TI, term infant; M, mother; I, infant; OMM, own mother's milk; DHM, donor human milk; CEN, complete enteral nutrition (150 ml/kg/day); RBW, recovery of birth weight; HM, human milk; FFQ, food frequency questionnaire.

Samples collected at home are stored at 4°C during a maximum of 24 h before their transport to the hospital on ice, where they are registered, aliquoted, labelled, and stored at −80°C until analysis. A HM and faeces aliquot is directly stored in a tube containing a microbiome preservative solution. For DHM, collection times respective to delivery are heterogeneous, since from each donor several aliquots are collected over time, pooled, and then subjected to Holder pasteurization in batches (i.e., 62.5°C during 30 min followed by rapid cooling to 4°C). The lactation time was estimated as the mean (standard deviation, SD) of time elapsed during the collection of different aliquots from one DHM batch, being 16 (SD 12) days.

Mothers' and infants' buccal swab samples are collected by thoroughly rubbing a flocked sterile swab up and down the inner side of both cheeks for 30 s each. Swabs are cut and stored in a sterile tube at −80°C until further analysis. Discarded arterial and venous blood from the umbilical cord is collected in EDTA blood sample tubes after the placenta is delivered and separated from the baby. Blood is centrifuged (1,300 × *g* for 10 min at 20°C) and the upper plasma layer is stored in opaque vials at −80°C until analysis. Mother's first morning urine is collected in a polypropylene container, and infant's urine is collected by placing sterile cotton pads in the diaper and, after urinating, squeezing them with a sterile plastic syringe into sterile tubes (see Figure 2). Mother's faeces are collected in a polypropylene container, and infant's faeces are collected directly from the diaper into sterile tubes using sterile tweezers.

**Figure 2 F2:**
[figure not shown]
Infants’ urine sample collection procedure. Sterile cotton pads are placed in the diaper (left); cotton pads soaked with urine are collected using sterile tweezers (middle); cotton pads are squeezed with a sterile syringe to collect the urine sample (right).

Mothers express milk using breast milk pumps following an SOP employed routinely in the hospital and the HM bank. The removable parts of the breast milk pump as well as the collection bottles are sterilized before their use. HM is collected at least three hours after breastfeeding. Mothers are required to wash their hands with soap and water and clean nipples with water. HM should be preferably expressed between 7 and 10 a.m., full expression of one breast is required (a minimum volume of 50 ml is recommended), and details regarding the extraction method (e.g., breast pump brand), date, and extracted volume are registered. For DHM samples, aliquots of each pooled DHM sample are collected before and after Holder pasteurization.

